#### Exit criteria

The exit criteria will be as follows: 1) participant request, 2) severe intra- or postoperative complications (i.e., wound complication, fracture, pulmonary embolism, etc.), and 3) intra-treatment side effects.

#### Randomization, allocation, and blinding

Orthopedic surgeons perform an initial screening of all patients who visit the department of orthopedic surgery due to degenerative knee OA. If the patients fulfill the eligibility criteria, they are referred to the principal study coordinator. The principal study coordinator performs the final eligibility assessment and asks for informed consent to enroll in this study. After their consent is obtained, participants are randomly assigned to each group in a 1:1:1 ratio to the conventional type, mixed type, and sitting type CPM groups. Block randomization will be used on groups of 12 to balance relocation into the intervention groups. After the initial allocation, the mixed CPM groups will be re-allocated into two groups. Mixed groups will receive combined interventions with two types of CPM machines and consist of two subgroups. One of the subgroups will receive intervention using the conventional type of CPM, followed by the sitting type of CPM, and the other subgroup will recieve intervention in the opposite order. This trial will be blinded to the assessor; after randomization, the allocation of participants will be confidentially managed by the principal study coordinator. All assessments will be conducted by a single trained physiotherapist in each hospital who is experienced in post-operative rehabilitation treatment and will be blinded to group allocation. Due to the nature of the study, participants will not be blinded and will be instructed not to communicate with any other researcher or physiotherapists about their interventions to minimize potential bias. If participants would like to discuss their rehabilitation program during the intervention, they will be able to do so with the unlabeled study coordinator.

#### Intervention protocol

All participants will undergo primary unilateral TKA at the Department of Orthopedic Surgery. The day before the surgery, all participants will be admitted to the ward. On the day of admission, basal demographics and outcomes will be collected by the assessor. All participants will be instructed on the interventions and post-operative exercise programs. The participants will start the intervention program on postoperative day 3, the day after the removal of the surgical site drainage system. Two CPM systems (sitting type and conventional type) will be applied to the allocated group of participants (Fig. 3). The pre-defined arc of the angles in the CPM machines will be determined according to the ROM of the knee joint measured before each intervention. The assessor will measure the maximal passive ROM of the knee joint by using a goniometer. The ROM measurements will be taken in all three positions: supine, sitting, and prone. The setting arc of the angles of the CPM machines will be determined by adding 10° to the highest measured values in the ROM in the three positions. On the first day, interventions will be applied twice daily for 30 min. From the second day to the end of the intervention, CPM machines will be applied twice a day for 1 h in each session, for a total of 2 h per day. All participants were mobilized as tolerated using a walker or crutches. Conventional CPM will be performed using the RCF1121® (CARETECH, Gumi-si, Gyeongsangbuk-do, Korea). The CPM machines used in the sitting position will be Resilion K20P® (HEXAR Humancare, Ansan-si, Gyeonggi-do, Korea). Each group of participants will receive 10 sessions of intervention using the allocated CPM machines. The group of participants planned using both types of CPM machines will consist of two sub-groups, one of which will receive intervention for 5 consecutive days using the conventional type of CPM, followed by 5 days of intervention using the sitting type of CPM, and the other sub-group will receive intervention in the opposite order.

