The authors hypothesized that these inconsistent results were due to the improper fitting of CPM machines with patients and measurement error of ROM between studies. Good to excellent inter-tester reliability and intra-tester reliability have been reported for measuring the ROM in the native knee using a simple goniometer [34, 35]. However, measuring the knee joint ROM in patients after TKA shows that 22% of the goniometer measurements had more than 5° differences from the true degree of knee flexion [36]. Therefore, we decided to apply more objective tools to measure the ROMs using a digital inclinometer and a hand-held dynamometer. Therefore, this randomized trial will be conducted using more objective measurement tools and exact prescribed pre-defined arc ranges than previous trials using CPM machines.

In conclusion, the randomized trial will provide evidence of using a new type of CPM machine applied in the sitting position to incorporate the use of CPM into post-operative rehabilitation guidelines in patients receiving TKAs.

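### The blinded assessor is also assigned the ROM reading that sets the CPM machine before each intervention, which weakens the blinding of a manually measured primary outcome

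*Protocol article*

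**What the plan says.** All references are to the Protocol article.

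- **Blinding.** Randomization, allocation, and blinding gives all assessments to a single trained physiotherapist in each hospital, blinded to group. Patients are not blinded and are told not to talk about their treatment with other researchers or physiotherapists. Range of motion in knee joint (under Primary outcome measurement) has a blinded physiotherapist measure ROM with a digital inclinometer at three time points, with passive ROM taken at 2 kgf on a dynamometer.
- **Machine setting.** In Intervention protocol the assessor collects the baseline outcomes. Further on in the same paragraph, the machine arc is "determined according to the ROM of the knee joint measured before each intervention", and "The assessor will measure the maximal passive ROM of the knee joint by using a goniometer". The arc is "determined by adding 10° to the highest measured values in the ROM in the three positions".
- **Instrument.** The Discussion reports that after knee replacement "22% of the goniometer measurements had more than 5° differences from the true degree of knee flexion". It gives this as the reason for choosing an inclinometer and dynamometer, and says that this trial will use more exact arc ranges than earlier ones.
- **Treating staff.** Predicted adverse events and monitoring names a treating physiotherapist.
- **Allocation.** "The principal study coordinator performs the final eligibility assessment and asks for informed consent to enroll in this study". After randomization, "the allocation of participants will be confidentially managed by the principal study coordinator". "Block randomization will be used on groups of 12", at 1:1:1.

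**The concern.** Assessor blinding is the main protection this open-label trial has against measurement bias. The primary outcome is obtained by a person moving the knee to the end of its range. The arms are easy to tell apart once anything is seen or said, because one machine is used sitting and the other lying. Placing the assessor beside the patient just before treatment, many times over, gives repeated chances for a remark, a visible machine or a prepared position to disclose the arm. If that happens, the later outcome reading could be influenced in a direction that differs between arms.

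There is also an inconsistency of instrument. The trial's rationale is that poor fitting and measurement error explain past results, yet the fit of the machine rests on the instrument that the Discussion describes as often inaccurate after this operation.

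**Working it through.** No figure in the article covers this point, so there is none to reproduce. The check sets the sections side by side and adds two small counts.

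**1. Is it the same person?** The blinding section assigns all assessments to one blinded physiotherapist per hospital. Intervention protocol uses the label assessor for the person collecting baseline outcomes and again, in the same paragraph, for the person taking the pre-intervention ROM. The natural reading is one person.

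**2. How often?** Intervention protocol uses the word intervention for a session: "On the first day, interventions will be applied twice daily for 30 min". It states 10 sessions per group. It also describes two applications a day and, for the mixed group, 5 + 5 = 10 days, which would be 2 × 10 = 20. These two counts are not reconciled in the text, so the range is 10 to 20 readings per patient. If intervention meant the whole course, there could be as few as one. The ROM outcome needs three visits, one of them before surgery. Pain and swelling add an assessment during the intervention period.

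**3. Does the reading reveal the arm?** No. The arc rule (highest of three positions plus 10°) is stated once and is not machine-specific. The text does not say that the assessor sets or sees the machine. The exposure comes from contact.

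**4. Instruments.** The arc is set by goniometer and the outcome is read by inclinometer. The Discussion's reason for avoiding the goniometer applies equally to the arc.

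**5. Secondary: predictability of a block of 12 (4:4:4).** Assume one list and a person who knows every earlier allocation in the block.

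- Expected number of allocations known with certainty (the closing run of one arm): 1 + 3/11 + (3/11)(2/10) + (3/11)(2/10)(1/9) = 1 + 0.2727 + 0.0545 + 0.0061 = 1.33, and 1.33/12 = 11.1%.
- Expected correct best guesses, with a, b, c places left per arm and n = a + b + c: G(a,b,c) = max(a,b,c)/n + (a/n)G(a−1,b,c) + (b/n)G(a,b−1,c) + (c/n)G(a,b,c−1), with G(0,0,0) = 0. This gives G(4,4,4) = 6.14, and 6.14/12 = 51.2%, against 33.3% by chance.
- For comparison, blocks of 6 give 20.0% certain and 56.1% right; blocks of 9 give 14.3% and 53.2%.
- Over 126 patients there are 126/12 = 10.5 blocks. Ten complete blocks give 10 × 1.33 ≈ 13 certain allocations. The half block adds none, because certainty arises only in the last four places of a block.

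**The case against.** The strongest reply is that the article's role labels are loose. Intervention protocol has the assessor collect demographics, while Outcome measurement and participants' timeline gives that task to a research delegate. The pre-session reading uses another instrument and the ROM outcome lists only three time points, so a different person may be meant. That is possible, but the text does not say so, and a site following it would use the blinded assessor.

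Three safeguards also stand: the instruction to patients, the common arc rule, and the 2 kgf standard with a digital reading. They limit the risk. They do not remove it, because the instruction depends on patients' compliance and no force standard is given for active ROM.

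Stronger readings are tempting, and the document does not support them:

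- **That blinding is defeated.** Nothing shows that the assessor learns the arm.
- **That the bias would be 2–3°, as large as the CPM effects quoted in the Background.** No estimate of assessor bias is given. Those effects compare CPM with control, not sitting with conventional CPM, and only a bias that differs between arms matters.
- **That allocation concealment is broken.** The coordinator manages allocations after randomization. Who generates and holds the unrevealed list is not stated and may be in the full protocol. That the block size never varies is inferred from the single size given, and 12 is less predictable than 6 or 9. Surgeons screen first, and no eligibility criterion concerns ROM.

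**Conclusion.** The point holds as a weakness in blinding. As written, the person who must stay blind is brought into the treatment routine some 10 to 20 times per patient, although the ROM outcome needs three visits and other staff are available. This rests on reading assessor as one role throughout and intervention as session. The resulting bias cannot be sized from the document. The goniometer conflict is real but separate: it concerns how the machine is set, not who is blinded.

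The allocation point is a caution, not a shown defect. The 51% against 33%, and the 1.3 certain allocations per block, are ceilings that assume one list and complete tracking of past allocations. They measure what could be guessed. They do not show that anyone selected patients.

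**What to change.** - **Roles.** State in Intervention protocol that the treating physiotherapist takes the pre-session ROM readings. Limit the blinded assessor to the scheduled outcome visits, held away from treatment sessions.
- **Instrument.** Reconcile the goniometer in Intervention protocol with the Discussion's reason for avoiding it and its claim of exact arc ranges.
- **Allocation.** Add one sentence saying who holds the unrevealed list and that this person does not judge eligibility.

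The cost is some extra time for the treating physiotherapist. One trade-off is that the arc would then rest on a reading by someone who knows the arm; the single written arc rule limits this. Trial status reports 68 patients recruited, so the role change can help at most 126 − 68 = 58 at that date. It applies to all arms alike, and its start date should be recorded. Drawing up a new randomization list at this stage is not clearly cheap: it would leave two schemes in one trial and may have to be reported to the review boards.

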**Fig. 3 Fig3:**
[figure not shown]
CPM machine set up. A conventional type of CPM machine (RCF1121®, CARETECH, Korea) (A-B), New type of CPM machine (Resilion K20P®, HEXAR humancare, Korea) (C-D) Each CPM machine will be applied to the participants according to the manufacturer's instruction

#### Outcome measurement and participants’ timeline

The primary outcomes are ROM of the knee joint at the end of the intervention and 3 months after TKA. The secondary outcomes are pain, and functional measurements included patient-reported outcomes and performance tests conducted at multiple time points up to 3 months after TKA. During the trials, the satisfaction questionnaire (additional file) will be administered only to participants of the mixed-type CPM group. Participants will be screened for adverse events from the time of informed consent to 3-months postoperatively. The study assessment schedule is illustrated in Fig. 4. Demographic details, including sex, age, height, weight, affected side, and medical history, will be surveyed preoperatively by the research delegate.

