**Fig. 4 Fig4:**
[figure not shown]
The patients' schedule of trial enrollment, interventions, and assessment. ROM, Range of motion; KSS, Knee society score; WOMAC, Western Ontario and McMaster Universities Osteoarthritis Index; 6MWT, 6-minute walking test; TUG, Timed up and go test. ^*^Both active and passive ROMs of knee flexion and extension will be measured. ^†^Isokinetic strength of knee flexion and extension measured at 60°/sec angular velocity using an isokinetic dynamometer (Systemic 4 Pro, Biodex Medical System, USA). ^‡^ Mixed-type CPM group only

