### Primary outcome measurement

#### Range of motion in knee joint

A blinded physiotherapist will measure active and passive ROM in the affected knee joint using a digital inclinometer (Dualer IQ electronic dual inclinometer system; JTECH Medical, UT, USA). Passive ROM will be measured with the patients in the supine, sitting, and prone positions. When evaluating the passive ROM, the assessor will mobilize the knee joint to the end of the range of applied force of 2 kgf using a handheld dynamometer (MicroFET2, Hoggan Health Industries, UT, USA). Active and passive ROM will be evaluated at three time points: the day before the surgery, after the intervention, and 3-months postoperatively.

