### Patients reported outcomes

Patient-reported outcomes will be measured using the Knee Society Score (KSS), Western Ontario and McMaster Universities Osteoarthritis Index (WOMAC), and Kujala Patellofemoral score [16–18].

The KSS is an objective scoring system to assess patient reporting outcomes in osteoarthritis, especially after TKA. The KSS is easy to obtain and concise. The Korean version of the KSS was validated in 2017 by Kim et al. [16], and participants will be assessed using this version.

The WOMAC score was developed by Bellamy et al. [19] and is widely applied to evaluate the status of lower-limb osteoarthritis. The WOMAC questionnaire consists of 24 questions in three domains. Pain (five items), stiffness (two items), and function (17 items) are evaluated on a total scale of 0–100; higher scores indicate greater disability. The Korean version of WOMAC was validated in 2001, and patients will be evaluated using this version [17].

The Kujala patellofemoral score will also be calculated. The Kujala patellofemoral score consists of 13-items with categories related to various levels of functional knee problems. All responses are summed to provide an overall index ranging from 0 to 100 points, with 100 points representing no disability [18].

Satisfaction questionnaires (Additional file 2) will be administered to participants in the mixed-type CPM group at the end of the intervention to compare conventional and new types of CPM machines.

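### A questionnaire given only to the mixed arm conflicts with the rule that one blinded physiotherapist per hospital conducts all assessments; followed literally, it would identify that arm before the 3-month ROM

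*Protocol article*

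**What the plan says.** On who assesses, the section on randomization, allocation and blinding states: "All assessments will be conducted by a single trained physiotherapist in each hospital". That person is described as "experienced in post-operative rehabilitation treatment and will be blinded to group allocation". The same section says that "the allocation of participants will be confidentially managed by the principal study coordinator", and that participants themselves are not blinded.

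On the questionnaire, the section on outcome measurement and timeline states that "the satisfaction questionnaire (additional file) will be administered only to participants of the mixed-type CPM group". The section on patient-reported outcomes, after describing the Knee Society Score, WOMAC and Kujala scores, adds that the form "will be administered to participants in the mixed-type CPM group at the end of the intervention to compare conventional and new types of CPM machines". The legend of Fig. 4, the assessment schedule, carries the footnote "Mixed-type CPM group only". The figure itself is not shown.

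On the primary measurement, the ROM section states: "A blinded physiotherapist will measure active and passive ROM in the affected knee joint using a digital inclinometer". It continues: "Active and passive ROM will be evaluated at three time points: the day before the surgery, after the intervention, and 3-months postoperatively". The outcome section counts both the end-of-intervention and the 3-month ROM as primary; the abstract names only the change to 2 weeks.

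**The concern.** These statements cannot all be followed as written. The form is listed among the patient-reported outcomes, and its legend belongs to the assessment schedule, so on the ordinary reading it is an assessment. The only rule on who conducts assessments gives them all to the blinded physiotherapist. Someone who gives a form to one arm only must know who is in that arm. The form's content, a comparison of two machines, also shows that the patient used both.

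Assessor blinding is the only masking the trial states. The same physiotherapist measures ROM again at 3 months, so an arm learned at the end of the intervention stays known for that later primary reading. It would also be known for any other measurement that physiotherapist takes at 3 months.

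**Working it through.** There is no stated figure to reproduce. The check is a side-by-side reading, a count, and a short bias argument.

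**Step 1: does the text place the form with the assessor?**
- Rule: one blinded physiotherapist per hospital conducts all assessments (randomization section). No exception is stated.
- Form: mixed arm only, end of intervention, compares the machines (outcome and patient-reported outcome sections; Fig. 4 legend).
- Administrator: not named. Both sections that mention the form use the passive voice.
- Result: the literal reading puts the form with the assessor, but this is inferred from the general rule and is not stated for the form itself.

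**Step 2: which ROM readings would be exposed, if the assessor handles or sees the form?**

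| ROM reading | Exposed? |
|---|---|
| Day before surgery | No; the form comes later |
| End of intervention | Only if the form precedes or accompanies the measurement; order not stated |
| 3 months | Yes, whatever the order at the earlier visit |

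**Step 3: how many patients?**
- Inputs: 42 per group (sample size section), three groups, 1:1:1 allocation.
- Total: 3 × 42 = 126.
- Identified as mixed: 42/126 = 33.3%.
- Remaining: 126 − 42 = 84, known only as not mixed. Sitting and conventional stay indistinguishable by this route.

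**Step 4: which comparisons would be biased?**
Let *b* be the mean shift in degrees that a knowing assessor introduces in the mixed arm, and *c* any shift in patients known only as not mixed. Because sitting and conventional patients cannot be told apart by this route, *c* is the same on average in both.
- Mixed versus sitting: bias = *b* − *c*
- Mixed versus conventional: bias = *b* − *c*
- Sitting versus conventional: bias = *c* − *c* = 0

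With *c* = 0 and an assumed *b* of 1, 2, 3 or 5 degrees, the two mixed-arm comparisons are biased by 1, 2, 3 or 5 degrees and sitting versus conventional by 0. The documents give no value for *b*, so this shows where bias would go, not how large it would be.

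**The case against.** The strongest reply is that nothing says the assessor handles the form. The principal study coordinator holds the allocations and is the natural person to give out an arm-specific questionnaire. A research delegate is named for demographics, so data collection need not rest with the assessor alone. The form may be self-completed, and participants are told not to discuss their intervention with other researchers or physiotherapists. Who hands out a form, and in what order, is often left to the full protocol, which is not shown.

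Much of this stands. A reader might infer that the assessor is in fact unblinded, is certain to identify the 42 patients, or talks through both machines with them. The document supports none of these: it names no administrator, gives no order within the visit and describes no such conversation. What does not stand is that this is merely missing detail. A universal rule is stated and an arm-specific assessment is scheduled under it without an exception. The research delegate is weak support for a separate administrator, because that role is given only preoperative demographics, and the intervention section has the assessor collecting baseline demographics and outcomes. Self-completion does not help if the assessor distributes, collects or sees the form.

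Two further limits are fair. Passive ROM is read with a digital inclinometer at a fixed 2 kgf measured by dynamometer, which narrows the room for bias; the assessor still moves the joint and takes the reading. A reader might also set a possible bias against the 2 to 3 degree effects in the Background. Those are CPM versus control, not mixed versus single machine, so they are no yardstick here.

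**Conclusion.** The point holds as a conflict in the text with a conditional consequence. If the assessor hands out, collects or sees the questionnaire, the mixed arm (42 of 126, 33%) is identified before the 3-month ROM, and before the end-of-intervention ROM only if the form comes first. The two comparisons involving the mixed arm would then be at risk of assessor bias of unknown size.

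A reader might conclude that the trial's main question is compromised. It is not, by this route: the stated hypothesis and purpose concern sitting versus conventional, and those patients would be known only as not mixed. The weight of the 3-month exposure also depends on which definition of the primary outcome governs, since the abstract and the outcome section differ.

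Confidence in the textual conflict is high; confidence that unblinding occurs in practice is moderate at most. The correction is worth making because it protects the only stated masking at almost no cost.

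**What to change.** Except the satisfaction questionnaire from the rule on assessments. State that the study coordinator, who already holds the allocations, gives it to mixed-arm participants and collects it after all end-of-intervention measurements are complete. State also that the assessor does not see it before that participant's 3-month assessment is done, which means keeping it out of the assessor's visit papers until then. If the sites already work this way, saying so resolves the conflict.

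The cost is one or two sentences in the protocol, a form held separately, and a few coordinator minutes per mixed-arm patient. No visit, staff post or treatment changes. The trial status section reports 68 patients recruited, so at that time 126 − 68 = 58 were still to be enrolled and could benefit in full. For those already enrolled, the sponsor should record who handled the form and when relative to the ROM measurement.
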